**Summary**:

Since December 2019 COVID-19 is dominating the life of the people of this universe. Its behavior also varied among the nations of the universe. The risk factor of adverse outcome of COVID-19 was determined. No biologic markers for the susceptibility of the infection is yet to be found. The relation of blood group and infection was found in several disease like cholera, severe malaria, severity of dengue, H-pylori infection have been elucidated. Genome wide Association Study of Severe Covid-19 with Respiratory Failure, GWAS Group detected cross-replicating associations with rs11385942 at locus 3p21.31 and with rs657152 at locus 9q34.2. The association signal at locus 9q34.2 coincided with the ABO blood group locus. Several studies also found some contradicting results in this regard.

So to observe the impact of ABO blood groups on the presentation and outcome of Confirmed COVID -19 infection, this study was conducted in the largest COVID19 dedicated hospital in Bangladesh. It would be a prospective cohort study. A cohort of the patients with RT-PCR positive COVID-19 patients since June 2020 till September 2020 will be included in this cohort. Their blood group will be determined. The clinical features, severity, time required to recover, conversion of severity, Persistence of RT-PCR positivity 14 days after initial positivity will be determined. They will be followed up for at least 30 days or hospital discharge which one is longer. Comparison will be made in different blood groups.

The primary outcome would be the duration required to have clinical improvement.

Data will be analyzed using SPSS 20. To compare the groups one way ANOVA was done for continuous variable, Chi square for categorical variables. For outcome assessment relative risk (RR) with 95% CI was measured for qualitative variable categorizing blood group A and non A. survival analysis by Kaplan-Meier curve was done for the duration of recovery. Result of the study and statistical analysis will be presented by tables, figures, graphs, diagrams, charts and photographs. All these will have own legends (i.e. title) and will be serially numbered. Discussion will be done on the basis of result obtained from the study and comparing with similar studies done at home and abroad. Summarization will be drawn after discussion. Conclusion will be drawn depending upon the results and discussion.

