**Primary Outcome Measure:**

- 1. Duration required to have clinical improvement

[Time Frame: 1 months]

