**Secondary Outcome Measure:**

1. Conversion to the next level of severity

Time Frame: 1 month]

1. Persistent positivity 14 days after initial positivity

[Time Frame: 14 days]

1. Severity of the disease

[Time Frame: 1 month]

1. Development of post COVID syndrome

[Time Frame: 1 month]

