**Clinical improvement Criteria**

1. Body temperature remains normal for at least 3 days (ear temperature is lower than 37.5 °C).

2. Respiratory symptoms are significantly improved.

3. Lung imaging shows obvious improvement in lesions.

4. There is no co-morbidities or complications which require hospitalization.

5. SpO2, >93% without assisted oxygen inhalation.

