**Subsequent follow up**

| Trait | Follow-up  Yes-1, No-2 | | | | | | | | | | | | | | | |
| --- | --- | --- | --- | --- | --- | --- | --- | --- | --- | --- | --- | --- | --- | --- | --- | --- |
|  | Day-15 | D16 | D17 | D18 | D-19 | D-20 | D-21 | D-21 | D-23 | D-24 | D-25 | D-26 | D-27 | D-28 | D-29 | D-30 |
| Fever |  |  |  |  |  |  |  |  |  |  |  |  |  |  |  |  |
| Cough |  |  |  |  |  |  |  |  |  |  |  |  |  |  |  |  |
| Running nose |  |  |  |  |  |  |  |  |  |  |  |  |  |  |  |  |
| Sputum |  |  |  |  |  |  |  |  |  |  |  |  |  |  |  |  |
| Respiratory distress |  |  |  |  |  |  |  |  |  |  |  |  |  |  |  |  |
| Sore throat |  |  |  |  |  |  |  |  |  |  |  |  |  |  |  |  |
| Hoarseness of voice |  |  |  |  |  |  |  |  |  |  |  |  |  |  |  |  |
| Chest pain |  |  |  |  |  |  |  |  |  |  |  |  |  |  |  |  |
| Diarrhoea |  |  |  |  |  |  |  |  |  |  |  |  |  |  |  |  |
| Vomiting |  |  |  |  |  |  |  |  |  |  |  |  |  |  |  |  |
| Anosmia |  |  |  |  |  |  |  |  |  |  |  |  |  |  |  |  |
| Anorexia |  |  |  |  |  |  |  |  |  |  |  |  |  |  |  |  |
| Headache |  |  |  |  |  |  |  |  |  |  |  |  |  |  |  |  |
| Confusion |  |  |  |  |  |  |  |  |  |  |  |  |  |  |  |  |

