**Radio-Imaging**

| **Trait** | **Findings** |
| --- | --- |
| Chest X-Ray  CT Chest | Normal/ Consolidation ( unilateral or bilateral) / Patchy opacity  Consolidation/ Ground Glass Opacity/nodule/ multifocal |

Post COVID symptoms:

Principal Investigators: ……………….. Date:

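### The post-COVID secondary outcome has the primary outcome's one-month frame, no defined start and one undated form line, so it cannot be separated from unresolved acute illness

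*Protocol*

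**What the plan says.** The primary outcome is "Duration required to have clinical improvement", with "Time Frame: 1 months". Among the secondary outcomes is "Development of post COVID syndrome", with "Time Frame: 1 month". The abstract for the National Research Ethics Committee repeats both. The secondary outcome on persistent PCR positivity counts its days from the first positive test, but the post-COVID outcome has no origin.

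The operational definitions cover confirmed infection, the severity levels, ARDS and clinical improvement. They give no symptom set, starting point or minimum duration for post-COVID syndrome, and no requirement of prior recovery. One improvement criterion is "Respiratory symptoms are significantly improved", so a patient can meet the primary outcome and still have symptoms.

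On the case record form, the only item for this outcome is the open line "Post COVID symptoms" after the imaging table, without a date or assessment day. Separately, the Clinical Feature grid and the "Subsequent follow up" grid record 14 symptoms daily from admission to D-30. Nothing links them to this outcome. The Summary says: "They will be followed up for at least 30 days or hospital discharge which one is longer".

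**The concern.** Whatever post-COVID is taken to mean, the acute illness must be over before it starts. Here both are read in the same month. If the month runs from admission, a patient who improves on day 8 has 22 days left in which to develop the outcome. One who improves on day 26 has 4. One who has not improved by day 30 either has none or is counted because the acute illness persists. The protocol does not say which.

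The time at risk is thus roughly 30 days minus the primary outcome. The Data analysis section compares qualitative outcomes between A and non-A by relative risk. If blood group changes the speed of recovery, that relative risk partly restates the primary result and could be reported as a separate finding on post-COVID symptoms.

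**Working it through.** The protocol gives no expected rate or sample size for this outcome, so there is no figure of its own to reproduce. The check asks what relative risk would appear if blood group had no effect on post-COVID symptoms.

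**Inputs from the protocol:** improved by day 12, 0.70 (A) and 0.90 (non-A), from the Sample size section, where the term used is cure; window, 30 days.

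**Assumptions:** days run from admission; after improvement, symptoms begin at the same constant rate λ in both groups, with λ = 0.5%, 1% or 2% per day; the shape of the recovery curve is varied.

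**Exponential recovery**

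- Hazard h = −ln(1 − p)/12. A: −ln(0.30)/12 = 0.1003 per day. Non-A: −ln(0.10)/12 = 0.1919 per day.
- Not improved at day 30, S = (1 − p)^(30/12). A: 0.30^2.5 = 4.9%. Non-A: 0.10^2.5 = 0.3%.
- Mean time after improvement = 30 − (1 − S)/h. A: 30 − 9.5 = 20.5 days. Non-A: 30 − 5.2 = 24.8 days.
- Risk of onset after improvement = 1 − S − [h/(h − λ)] × [exp(−30λ) − S]. For A at λ = 0.01: 1 − 0.0493 − 1.1107 × (0.7408 − 0.0493) = 0.183.

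| λ per day | Onset after improvement, A vs non-A | RR | Adding those not improved at day 30, A vs non-A | RR |
|---|---|---|---|---|
| 0.5% | 9.7% vs 11.6% | 0.83 | 14.6% vs 12.0% | 1.22 |
| 1% | 18.3% vs 21.9% | 0.84 | 23.2% vs 22.2% | 1.05 |
| 2% | 32.7% vs 38.8% | 0.84 | 37.6% vs 39.1% | 0.96 |

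**Other shapes with the same day-12 proportions.** The exponential curve puts 26% of A and 44% of non-A as improved by day 3. That is hard to square with a criterion of normal temperature for at least three days plus better imaging. I therefore used S(t) = exp{−[(t − L)/s]^k} for t > L, with s chosen so that S(12) = 0.30 or 0.10, and integrated numerically. The three RRs in a cell are for λ = 0.5%, 1% and 2%.

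| Recovery shape | RR, onset after improvement only | Not improved at day 30, A vs non-A | RR, adding those not improved |
|---|---|---|---|
| Exponential (k = 1, L = 0) | 0.83, 0.84, 0.84 | 4.9% vs 0.3% | 1.22, 1.05, 0.96 |
| 3-day lag (k = 1, L = 3) | 0.86, 0.86, 0.87 | 2.7% vs 0.1% | 1.10, 0.99, 0.94 |
| Weibull (k = 2, L = 0) | 0.89, 0.89, 0.90 | 0.05% vs about 0% | 0.89, 0.89, 0.90 |
| Weibull, 3-day lag (k = 2, L = 3) | 0.91, 0.91, 0.92 | about 0% in both | 0.91, 0.91, 0.92 |

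With no true effect, the relative risk lies between 0.83 and 0.92 if only onset after improvement counts. It falls on either side of 1 if unresolved illness counts as well.

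**The case against.** Four points on the other side deserve weight.

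*The bias is conditional.* A reader might infer that the outcome is biased by the primary outcome as such. The documents do not support that. The distortion needs recovery time to differ by blood group, which is what the study is testing. The 0.70 and 0.90 are planning assumptions. This stands. What does not depend on it is that the outcome cannot be classified as written.

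*The direction is not fixed.* A reader might also infer that group A must look harmed once unresolved illness is counted. The tables show otherwise: 37.6% vs 39.1% at 2% per day under the exponential curve, and a relative risk below 1 at every rate under both Weibull shapes.

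*The distortion is modest beside sampling error.* With 126 A and 252 non-A (378 at 1:2), 18.3% vs 21.9% would carry a 95% interval for the relative risk of about 0.54 to 1.29, and such a difference would be declared significant only about 13% of the time. This is fair. It limits the risk of a false positive claim but does not make the estimate interpretable.

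*The form holds more than one undated line, and follow-up may run past 30 days.* Both are true. The daily grids could partly separate persisting from new symptoms, but the protocol does not tie them to this outcome, and they have no row for fatigue, malaise or muscle pain. Follow-up beyond 30 days is guaranteed only to patients still in hospital, which ties observation time still more closely to the acute course.

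Nor can this simply be left to an analysis plan. The time frame and the form are set here, and onset dates cannot be recovered from an undated line.

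**Conclusion.** The point holds as one of outcome definition and data capture, and should be corrected. That the outcome cannot distinguish unresolved acute illness from post-COVID symptoms follows from the text alone.

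The effect on the A versus non-A comparison is conditional and illustrative. It requires recovery to differ by blood group as the sample-size section assumes, and it rests on assumed recovery shapes, a constant onset rate of 0.5 to 2% per day and a month counted from admission. Under those assumptions the spurious relative risk is about 0.83 to 0.92 when only onset after improvement counts. When unresolved illness also counts, neither its direction nor its size can be settled from the protocol.

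**What to change.** In the Secondary Outcome Measure list, in both the main protocol and the ethics committee abstract, replace the outcome with symptom status at day 30 for every patient.

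- Take it from the D-30 column of the existing symptom grid. Keep the post-COVID free-text line but date it to D-30, so that fatigue, malaise and muscle pain are captured. Deleting the line would lose them.
- Report three categories by blood group: improved and symptom-free; improved with symptoms; not yet clinically improved. Do not label the last as post-COVID syndrome.
- Report the time from clinical improvement to day 30 by blood group, and read the improved-with-symptoms comparison in its light. A fixed assessment day does not remove the dependence on time since improvement; it only makes it visible.

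The cost is a change of wording in two places and a date on one form line. The grid entries are already scheduled, and the primary outcome already requires the improvement date. The downside is that the study can claim only day-30 symptom status, not a post-COVID syndrome outcome.

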**Data collection technique:**

Data will be collected by assigned trained data collectors (Physician).

Patient will be enrolled according to defined inclusion and exclusion criteria in the current research. Informed written consent will be obtained from the participants. Each participants participating in the trial will be uniquely identified, and information such as his name, address is recorded in the trial 'subject number list'.

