**3. RATIONALE:**

Covid-19 is an emergent pandemic, threatens the life of millions of the people throughout the globe. The severity, outcome and susceptibility varies among the nations, race and individuals. Biologic markers of COVID-19 infection is still uncertain. Several studies revealed blood group A is most susceptible. The studies were performed with the affected patients only. This study Aim to observe the impact of different blood groups on presentation and outcome of confirmed COVID-19 infection. It would help us to detect a biologic marker for the susceptibility and outcome of COVID-19 infection.

1. **METHODOLOGY:**

Study type: Prospective cohort

Sample size:

Proportions to cure from COVID-19 by day-12 in group-1(blood group A) and group-2 (blood group Assuming expected B, O, AB) are 0.70 and 0.90 respectively. Thus we need a total of 378 samples at 1:2 ratio, and, that would provide a power of at least 90% at two tailed test where p value less than 0.05 to detect significant difference between the groups. Considering 10% dropout, we need 416 samples in total.

$$n=\frac{r+1}{r}\frac{p^{*}\left( 1-p^{*} \right){(Z_{\beta}+Z_{\frac{\alpha}{2}})}^{2}}{{{(p}_{1}- p_{2})}^{2}}$$

r = ratio of group-1 and group - 2

p*= Average of proportion

Z_α/2_ = Level of significance

Z_β_ = Power of the test

p_1_ - p_2_= Effect size

p_1_ = Proportion in group - 1

p_2_ = Proportion in group - 2

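### Nothing keeps blood group from the physicians who collect outcome data, although two of the five improvement criteria are unscaled judgements and the plan expects group A to do worse

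*Protocol*

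**What the plan says.** The primary outcome is "Duration required to have clinical improvement", over one month. Under Operational definition, the Clinical improvement Criteria list five items. Two are measured: temperature ("Body temperature remains normal for at least 3 days", with an ear-temperature cut-off) and oxygen saturation above 93% without assisted oxygen. Two are judged with no scale, threshold or named reader: "Respiratory symptoms are significantly improved" and "Lung imaging shows obvious improvement in lesions". The remaining item, "There is no co-morbidities or complications which require hospitalization", also leaves some room for judgement. The list does not say whether all five must be met.

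On who collects the data, Data collection technique says "Data will be collected by assigned trained data collectors (Physician"; the ethics-committee abstract (Part-G) repeats it. On the exposure, the Summary says "Their blood group will be determined", with no statement of when, by whom, or who sees the result.

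The direction expected for recovery is in the sample-size paragraph: 0.70 cured by day 12 in group A and 0.90 in groups B, O and AB. The Rationale adds "Several studies revealed blood group A is most susceptible", which concerns susceptibility rather than recovery. Data analysis sets A against non-A, with relative risks for qualitative outcomes, and gives Kaplan-Meier curves for the duration of recovery.

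**The concern.** An assessor who knows the exposure and the hypothesis may be slower to call a group A patient improved when the call rests on wording without a threshold. That is differential misclassification, in the direction the study is planned to detect and on its primary outcome. If all five criteria must be met, a late call on one judged item delays the event even when temperature and saturation have settled. The secondary outcomes that need clinical judgement (severity, conversion to the next level, post-COVID syndrome) are open to the same influence.

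Masking is unusually easy here. ABO group is a laboratory result, and no eligibility or improvement rule in the protocol uses it. Who rates outcomes and what they know is a matter of data collection, so it belongs in the protocol section that covers data collection.

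**Working it through.** **1. Is there a safeguard?** Setting the sections side by side:
- Data collection technique (main text and Part-G): physicians collect; nothing on masking to blood group, no independent assessor.
- Clinical improvement Criteria: no reader or threshold for the symptom and imaging items.
- Abstract summary for Ethical Committee: data are coded, locked and open to research personnel only. This protects confidentiality; it does not separate exposure from outcome.
- Case Record Form: daily yes/no symptoms, daily temperature and oxygen saturation to day 30, laboratory values and one set of imaging findings. There is no ABO field, and none for improvement date or severity level.

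The form itself would not reveal the group. Equally, nothing says where the group is held, and the decision that a patient has improved has no recorded place or author.

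**2. How sensitive is the comparison?** The protocol gives no figure on this point, so this is an illustration.

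Inputs from the protocol: total 378 at 1:2, that is 378/3 = 126 in A and 252 in non-A; two-sided 0.05.

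Assumptions not in the protocol: no true difference; 80% improved by day 12 in both groups; judgement lowers the recorded proportion in A only, by a shift m.

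With p_B = 0.80 and p_A = 0.80 − m:
- p̄ = (126·p_A + 252·p_B)/378
- SE0 = √[p̄(1−p̄)(1/126 + 1/252)]
- SE1 = √[p_A(1−p_A)/126 + p_B(1−p_B)/252]
- P(reject) = Φ((m − 1.96·SE0)/SE1) + Φ((−m − 1.96·SE0)/SE1)

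For m = 0.05: p̄ = (94.5 + 201.6)/378 = 0.7833; SE0 = 0.0450; SE1 = 0.0461; P = Φ(−0.83) + Φ(−3.00) = 0.204 + 0.001 = 0.205.

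| Shift in A | P(false significance), base 0.80 | base 0.90 |
|---|---|---|
| 0 | 0.050 | 0.050 |
| 3 points | 0.108 | 0.152 |
| 5 points | 0.205 | 0.308 |

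**3. Does this carry over to the duration endpoint?** Only loosely. Day-12 cure appears only in the sample-size text; the primary outcome is a time. A simulation with a log-rank test (which the protocol does not name), gamma-distributed times (shape 2 or 4) with 80% improved by day 12, 126 versus 252 patients and no true difference gives:
- 10% of A patients called two days late: about 5-7% false positives.
- 25% of A patients called one day late: about 5-7%.
- Every A patient called one day late: about 26-44%. This corresponds to a day-12 shift of 4-6 points.

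Occasional late calls barely matter; a systematic lag does.

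**The case against.** The best reply is that the route to bias is inferred. The protocol does not say that the collecting physicians see the blood group, that they are told the expected direction, or that they are the ones who apply the improvement criteria. The form carries no ABO result. Two criteria are measured. The Summary and Introduction call earlier findings contradictory, and the Introduction links non-A type to venous thromboembolism, which points the other way. All of this stands, and it limits the point to an unprotected risk.

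Three stronger readings are tempting and not supported:
- *The assessors are unmasked.* The text is silent; it does not say they know. But absence of an ABO field is not a masking procedure, and no other assessor is named.
- *The bias could not be addressed afterwards.* Temperature and saturation are scheduled daily to day 30, so an analysis free of the judged items is possible. It is not the full composite, but it tests for this bias.
- *The false-positive rate would be very high.* Shifts of 8 or 10 points would give 42% or 58% at a base rate of 0.80, but nothing in the documents supports shifts of that size, and they describe a day-12 proportion rather than a duration.

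That the study is observational does not answer the point: assessors can be kept unaware of a laboratory exposure in a cohort.

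**Conclusion.** The point holds as a worthwhile, inexpensive improvement, not as a demonstrated bias. The protocol leaves blood group open to those who collect outcome data, defines two of five improvement criteria by unscaled judgement, and plans on group A doing worse. The size of any resulting bias is unknown. The rise from 5% to about 11-21% is illustrative and rests on an assumed 3- to 5-point shift, a base rate of 0.80, 126 versus 252 patients and no true effect. That the collecting physicians also decide improvement is an inference from Data collection technique.

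**What to change.** 1. In Data collection technique, in both places, state that the ABO result is held on a separate sheet keyed by patient ID and linked to outcome data only after the improvement date and severity level are entered. Add those two fields to the Case Record Form, which now has neither.
2. State that whoever judges the respiratory-symptom and imaging criteria does so without the ABO result.
3. Record when the group was already known to the assessor and report this descriptively by blood group. Do not drop these patients from the main analysis: the group may have become known through events after enrolment that are related to severity, so dropping them could introduce selection.
4. Add a sensitivity analysis of time to meeting only the measured criteria (temperature and oxygen saturation). The daily readings are already scheduled, but the form does not show whether saturation was read on supplemental oxygen, so a tick box is needed.

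Cost: one extra sheet, a few form entries, a linking step and a short procedure; no added test or staff. Some groups will be known anyway, so protection is partial.

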**Data analysis**:

To compare the groups one way ANOVA was done for continuous variable, Chi square for categorical variables. For outcome assessment relative risk (RR) with 95% CI was measured for qualitative variable categorizing blood group-A and non-A (Group-B, AB, O). Survival analysis by Kaplan-Meier curve was done for the duration of recovery.

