**Inclusion Criteria:**

- At least 18 years of age
- COVID-19 infection, confirmed by polymerase chain reaction (PCR) test
- Mild to moderate COVID-19 infection

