**Uncomplicated (mild) Illness**

These patients usually present with symptoms of an upper respiratory tract viral infection, including mild fever, cough (dry), sore throat, nasal congestion, malaise, headache, muscle pain, or malaise. Signs and symptoms of a more serious disease, such as dyspnea, are not present.

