**Severe Pneumonia**

Fever is associated with severe dyspnea, respiratory distress, tachypnea (> 30 breaths/min), and hypoxia (SpO2 < 90% on room air). However, the fever symptom must be interpreted carefully as even in severe forms of the disease, it can be moderate or even absent. Cyanosis can occur in children. In this definition, the diagnosis is clinical, and radiologic imaging is used for excluding complications.

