**Acute Respiratory Distress Syndrome (ARDS)**

The diagnosis requires clinical and ventilatory criteria. This syndrome is suggestive of a serious new-onset respiratory failure or for worsening of an already identified respiratory picture. Different forms of ARDS are distinguished based on the degree of hypoxia. The reference parameter is the PaO2/FiO2:

- Mild ARDS: 200 mmHg < PaO2/FiO2 ≤ 300 mmHg. In not-ventilated patients or in those managed through non-invasive ventilation (NIV) by using positive end-expiratorypressure (PEEP) or a continuous positive airway pressure (CPAP) ≥ 5 cmH2O.
- Moderate ARDS: 100 mmHg < PaO2/FiO2 ≤ 200 mmHg.
- Severe ARDS: PaO2/FiO2 ≤ 100 mmHg.

When PaO2 is not available, a ratio SpO2/FiO2 ≤ 315 is suggestive of ARDS.

Chest imaging utilized includes chest radiograph, CT scan, or lung ultrasound demonstrating bilateral opacities (lung infiltrates > 50%), not fully explained by effusions, lobar, or lung collapse.

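### Severity is defined in rising levels, but the methods the protocol names for a categorical outcome either ignore that order or require collapsing to two levels

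*Protocol*

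**What the plan says.** The Protocol's Secondary Outcome Measure section lists "Severity of the disease" and, separately, "Conversion to the next level of severity", both over one month. The operational definitions give a ladder of states: mild illness, moderate pneumonia, "Severe Pneumonia", then ARDS, where "Different forms of ARDS are distinguished based on the degree of hypoxia". That makes four levels, or six if the three ARDS grades are counted separately. Entry is restricted to the two lowest ("Mild to moderate COVID-19 infection").

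The Data analysis section pairs one-way ANOVA for continuous variables with "Chi square for categorical variables". It then adds: "For outcome assessment relative risk (RR) with 95% CI was measured for qualitative variable categorizing blood group-A and non-A". The same text stands in the Part C Summary and in the abstract for the national ethics committee. No test that uses the order of categories is named. The protocol does not say how many severity levels are analysed, and it makes no power statement for severity.

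**The concern.** A Pearson chi-square gives the same result however the severity columns are arranged. It spreads its sensitivity over every possible pattern of difference, while the pattern of main interest here is that one blood group tends towards worse levels. With more than two levels it usually needs a larger shift to reach significance than a test that uses the order, and it does not summarise the shift in one number. The relative risk does give one number with an interval, but only after the levels are cut to two, which discards information in another way. At stake is a moderate, consistent association between blood group and severity being missed, although the planned data could have shown it.

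**Working it through.** **Inputs from the Protocol.** The sample size section gives 378 patients at 1:2. Its own formula with r = 0.5, p* = (0.70 + 0.90)/2 = 0.80, two-sided 0.05 and 90% power gives (1.5/0.5) × 0.80 × 0.20 × (1.960 + 1.282)² / 0.20² = 126.1. Taken as the smaller group, that is 126 A and 252 non-A, total 378. This calculation concerns cure by day 12, so only the group sizes are borrowed. The protocol has no power figure for severity to reproduce.

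**Assumed.** The severity distribution in non-A patients, and a common odds ratio for worse severity in group A at every cut of the scale.

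**Step 1: analytic check.** If the shift lies wholly along the order, both tests have the same noncentrality λ but different degrees of freedom. Power = P(χ² with k df and noncentrality λ exceeds its 5% critical value). For two groups and 80% power on the 1-df ordinal test, λ = (1.960 + 0.842)² = 7.85.

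| Levels | Chi-square df | Chi-square power | Loss (points) |
|---|---|---|---|
| 2 | 1 | 80.0% | 0 |
| 3 | 2 | 70.9% | 9 |
| 4 | 3 | 64.5% | 15.5 |
| 6 | 5 | 55.5% | 24.5 |

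For all four blood groups (ordinal test on 3 df, 80% power), the losses are 11, 19 and 30 points for 3, 4 and 6 levels.

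**Step 2: simulation.** Four levels, 126 against 252, two-sided 0.05, 20,000 replicates; Pearson chi-square against Wilcoxon with midranks. Type I error was 5% for both tests.

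| Non-A mild/moderate/severe/ARDS (%) | Odds ratio | Chi-square | Rank test |
|---|---|---|---|
| 45/40/11/4 | 1.6 | 48% | 64% |
| 45/40/11/4 | 1.7 | 59% | 74% |
| 45/40/11/4 | 1.8 | 68% | 82% |
| 60/30/7/3 | 1.7 | 56% | 71% |
| 30/50/15/5 | 1.7 | 58% | 73% |

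In these three distributions the gap is 7 to 8 points at odds ratio 1.3, about 10 at 2.0 and about 2 at 2.5. A more skewed distribution, 70/20/7/3, gives 6 points at 1.3 and 15 at 1.7.

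**Step 3: the relative-risk route.** Cutting severity at severe or worse, at odds ratio 1.7, gives 50%, 39% and 56% power in the distributions 45/40/11/4, 60/30/7/3 and 30/50/15/5. The rank test gives 74%, 71% and 73%. In each case the cut is also below the four-level chi-square.

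**Step 4: where the ordering does not help.** With A at 50/25/13/12 and non-A at 55/27/13/5, so that the excess sits mainly in ARDS, chi-square has 52% power and the rank test 30%. With A at 55/25/8/12 against the same non-A distribution, the figures are 63% and 7%.

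**The case against.** **Nothing is stated wrongly.** Chi-square is a valid test and keeps its error rate. Severity is one of four secondary outcomes with no power claim, and an analysis plan that is not shown could name an ordinal method. This stands and limits the point to efficiency. The protocol nevertheless does name a method for categorical variables, and that method sits poorly with its own ordered definitions.

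**A fixed 15-point loss.** A reader might infer that the plan commits severity to a test on 3 degrees of freedom and so gives up 15 points. The documents do not support this. The sentence is generic, and the number of levels is left open. Chi-square is paired with ANOVA, which suggests a comparison across blood groups rather than A against non-A. The 15 points belong to one assumed setting. At the odds ratio implied by 0.70 against 0.90, which is (0.9/0.1)/(0.7/0.3) = 3.86 and concerns cure, both tests have about 100% power.

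**No effect size at all.** A reader might also infer that the plan offers none. It offers a relative risk with a 95% confidence interval for A against non-A. What is lacking is one that uses the whole scale. If severity were analysed in two levels by intent, ignoring order would cost nothing; Step 3 shows what reaching two levels by collapsing four would cost.

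**Chi-square can win.** Step 4 shows this is true when the difference is confined to one end of the scale. It is a reason to keep chi-square as a supplement, but a weak one for making it the main test of a question about better or worse outcome.

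**Conclusion.** The concern holds as a point of efficiency on a secondary outcome. The severity levels are ordered by the protocol's own definitions, and neither named method uses that order. Under assumed four-level distributions with a common odds ratio, at 126 against 252, chi-square loses about 7 to 16 points of power to a rank test for odds ratios 1.3 to 2.0, with the largest losses (about 15) at 1.6 to 1.8. The loss is about 2 points at 2.5 and nil with two levels. Collapsing to severe or worse does not recover it. None of these sizes can be derived from the protocol alone, because it states no severity distribution, effect or number of analysed levels. Nothing here makes the chi-square invalid or affects the primary outcome.

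**What to change.** In the Data analysis section, and in its repeats in the Part C Summary and the national ethics committee abstract, state which severity levels are analysed. Compare them with a test that uses the order: Wilcoxon rank-sum for A against non-A, Kruskal-Wallis for the four blood groups, or a proportional-odds model reporting one odds ratio with a 95% confidence interval. Keep chi-square for unordered variables and, if wanted, as a supplementary test for severity.

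The analysis change takes a sentence or two and no extra patients. There are two small costs. First, the case record form has no field for severity level. It records oxygen saturation but not PaO2 or FiO2, on which the ARDS definition rests, so the level must be recorded directly or a derivation written down. Second, the odds-ratio model needs a check of proportionality; the rank tests do not.
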